# Metacognitive therapy and work-focused interventions for patients on sick leave due to anxiety and depression: study protocol for a randomised controlled wait-list trial

**DOI:** 10.1186/s13063-021-05822-4

**Published:** 2021-11-27

**Keywords:** Sick leave, Anxiety, Depression, Work-focused interventions, Metacognitive therapy, Cost-effectiveness, Randomised controlled trial

## Abstract

**Background:**

Common mental disorders such as depression and anxiety are major contributors to the global burden of disease. Affected individuals suffer reduced quality of life, impaired functioning and reduced capacity to work. Maintaining employment is an important determinant for health and wellbeing, and the economic impact of depression and anxiety is a significant societal expense. Treatments providing effective symptom reduction and helping patients return to work (RTW) would thus have substantial public health benefits. The present study will explore the effectiveness of metacognitive therapy (MCT) and work-focused interventions on reducing symptoms and increasing RTW rates for patients on sick leave due to depression and anxiety.

**Methods:**

The study is a randomised controlled wait-list trial (RCT; *N* = 240). The intervention group will receive protocol-based MCT and work-focused interventions immediately after inclusion. The control condition is a wait-list control group. All patients will receive up to 12 weekly sessions. The study context is a Norwegian outpatient clinic part of a national programme aimed at reducing sick leave. The co-primary outcomes are change in RTW and symptoms of depression and anxiety at the end of treatment. In addition to self-report, sick leave will also be collected from national registries from 2 years prior to intervention to 4 years after intervention. Symptoms of depression and anxiety will be collected by self-report at pre- and post-treatment and at 6 and 12 months follow-up after treatment. A cost-effectiveness analysis will use total cost and quality-adjusted life-years as the secondary outcomes.

**Discussion:**

There is broad consensus on the importance of identifying treatment that effectively reduces depression and anxiety symptoms and aids RTW. This study is an important contribution to the field as it is the first RCT on MCT and work-focused interventions for patients on sick leave due to anxiety and depression.

**Trial registration:**

ClinicalTrials.gov NCT03301922. Registered on October 4, 2017.

**Supplementary Information:**

The online version contains supplementary material available at 10.1186/s13063-021-05822-4.

## Background

Recent estimates indicate that mental illness may account for nearly a third (32.4%) of total years lived with disability, making it the main contributor to the global burden of disease [1]. Common mental disorders such as depression and anxiety are the most prevalent mental illnesses and thus account for the largest share of the disease burden [2, 3]. Affected individuals suffer reduced quality of life, including functional impairment [4]. In Europe, depression is responsible for 13.7% of all years lived with disability, and anxiety disorders likely have a similar impact [5, 6]. In 2018, the economic cost of mental disorders in Europe was estimated to be €600 billion a year, 40% of which was due to reduced employment and lost productivity [7].

In addition to the economic cost, loss of employment is detrimental to health and wellbeing, and work impairment is associated with negative health outcomes [8]. Sick leave may sometimes be warranted, but even short-term sick leave may increase the risk of future long-term absence [9]. Cardinal symptoms of depression and anxiety are avoidance and withdrawal, behaviours that may be reinforced by absence from social arenas such as the workplace. There is therefore broad agreement that treatment for patients on sick leave due to depression and anxiety should aim to help patients remain at work, or in the case of sick leave, return to work (RTW) [10].

Cognitive behavioural therapy (CBT) is effective for treating depression and anxiety symptoms [11], but its impact on work status is most likely limited. One meta-analysis from 2017 found that standard CBT without work-focused interventions had no impact on the work status of patients with depression and anxiety [12]. This is consistent with an evaluation of mental health and work conducted by the Organisation for Economic Co-operation and Development (OECD): in treatment for sick-listed workers, work status is neither a core competency, priority or outcome measure in traditional psychotherapy [13]. Results from a recent randomised controlled trial evaluating “Prompt Mental Health Care”, a programme for treating common mental disorders, are consistent with this conclusion. In this study, CBT was more effective than treatment as usual for reducing symptoms of anxiety and depression, but did not improve rates of return to work [14].

Attempts have thus been made to integrate work-focused interventions with standard treatment of common mental disorders [15]. To our knowledge, one of the first RCTs on treatment for patients with common mental disorders that include RTW as an outcome measure was conducted in the Netherlands in 2006, concluding that work-focused CBT (W-CBT) lead to earlier RTW [16]. Further research in the Netherlands found that adding work-focused interventions to treatment yielded effective symptom reduction, reduced the number of working days lost and had a high probability of being cost-effective [17]. A 2012 comparative outcome study found that patients who received W-CBT returned to work faster than participants receiving only CBT [18]. Since then, further support for W-CBT has been found in German and Swedish studies [19, 20]. Recently, reviews of the literature on work-focused treatment found strong evidence that CBT paired with work-focused interventions can reduce the duration of and costs due to sick leave, and recommends further implementation of such programmes [12].

Despite the encouraging results, combining psychotherapy with work-focused interventions is still in its infancy. A systematic review and meta-analysis from 2016 [21] indicated that there is a high degree of heterogeneity between studies. This is related to the type of therapies used, which work interventions are used, how they are implemented and how the outcomes are measured, making comparison difficult [21]. Additionally, a clear description of the therapy, the work focused interventions and adherence is often lacking [22]. This underlines the need for preregistered high-quality randomised controlled trials and publications of study protocols [22].

In addition to the need for more rigorous studies, there is also room for improving treatment outcomes [22]. The majority of the work-focused treatment studies have been modelled on CBT as the evidence for its efficacy in treating depression and anxiety symptoms is well explored [11]. The research in general shows significant improvement in symptoms in approximately 50% of patients but this masks considerable variability in outcomes across studies [23, 24]. Furthermore, a treatment where half of the patients do not get significantly better leaves considerable room for improvement. Follow-up of 1- and 2-year relapse rates show that 25–50% of patients treated for depression relapse, and the corresponding number for anxiety is about 15% [25, 26]. In recent years, metacognitive therapy (MCT) has shown excellent results in treating depression and anxiety [27]. Recent studies on MCT in Norway have shown recovery rates of 65% and 70% for anxiety and depression, with similar rates at 1 and 3-year follow-up [28–31]. In Denmark a comparison of MCT with CBT for depression showed that MCT was superior, achieving a 74% recovery rate compared with 52% in CBT [32]. A separate Norwegian study also showed that metacognitions, a central construct in MCT, may also predict work status [33]. This indicates that MCT is a very promising treatment which may represent a significant step forward in terms of recovery from depression and anxiety and may be more effective than existing approaches.

An observational study at Diakonhjemmet Hospital in Norway, which included work-focus interventions found that significantly more patients returned fully to work at end of treatment in the intervention group than in the wait-list group (41.4% versus 26.3%) [34]. The findings from this study are promising, warranting further exploration in a RCT.

To date, no study has investigated Metacognitive therapy (MCT) and work-focused interventions together. This waitlist RCT primarily evaluates the changes in symptoms of depression and anxiety, and percentage of sick leave, and secondarily whether the treatment is cost-effective. The main hypotheses to be tested are:
MCT plus work-focused interventions will be superior to the wait-list condition in reducing symptoms of anxiety and depression and the percentage of sick leave. Results will examine post-treatment and for the intervention group at 6 and 12 months follow-upMCT plus work-focused interventions will be cost-effective when compared with the wait-list condition. Self-report data on the percentage of sick leave will examine post-treatment, 6 and 12 months follow-up, in addition with the national register data span from 24 months prior to treatment and 48 months after ending the treatment

## Methods

### Primary objectives

The primary objective of the study is to examine the impact of MCT plus work-focus interventions on symptoms of depression and anxiety and percentage of sick leave at end of treatment. Other measurement points will be included in secondary objectives. Self-report data will be collected at initial assessment, start and end of treatment as well as at 6 and 12 months follow-up. Data from the national registry related to percentage of sick leave is collected up to 24 months prior to and 48 months after treatment. A schematic overview of measurements and endpoints are included in Fig. 2. The following measures will be used:
Changes in the degree of sick leave recorded from National registries (time frame: from 2 years prior to intervention to 4 years after intervention).Changes in the degree of sick leave from patient self-report (time frame: from pre-treatment, to post-treatment (12 weeks), and at 6 months and at 1 year follow-up).Changes in anxiety symptoms as recorded by Beck Anxiety Inventory (BAI) [35] (time frame: from pre-treatment to post-treatment (12 weeks) and at 6 months and 1 year follow-up).Changes in depressive symptoms measured by Beck Depression Inventory II (BDI-II) [36] (time frame: from pre-treatment to post-treatment (12 weeks) and at 6 months and 1 year follow-up).

BDI-II and BAI are self-reported measures. For the percentage of sick leave, both national registry data will be collected from the National Labour and Welfare administration in addition to self-report.

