### Secondary objectives

The secondary objective of the study is to determine whether the treatment is cost-effective compared to the wait-list condition and to examine other exploratory outcome measures. The questionnaires will be collected at screening, first treatment session and last treatment session. Follow-up questionnaires will be collected at 6 and 12 months post-treatment. The exception is change in diagnoses which will be evaluated by clinical interview at screening, before the first treatment session and after the last treatment session.

Measurements for the study’s secondary objective:
Changes in quality of life as measured by the EQ-5D-5L [37]Changes in metacognitions as measured by the Metacognitions Questionnaire 30 (MCQ-30) [38]Changes in bullying and victimisation as measured by the Negative Acts Questionnaire [39].Changes in work-related self-efficacy as measured by the Return to Work Self-Efficacy questionnaire (RTW-SE) [40].Changes in resilience as measured by The Resilience Scale for Adults (RSA) [41]Changes in subjective health complaints as measured by the Subjective Health Complaints questionnaire (SHC) [42].Change in diagnoses as measured by the Mini-International Neuropsychiatric Interview (M.I.N.I.) [43].

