### Randomisation and blinding

After the initial screening session, eligible patients will be randomised using WebCRF, a web-based program provided by the Unit for Applied Clinical Research at the Norwegian University of Science and Technology (NTNU). The block randomisation is stratified on gender and degree of sick leave. The study will include 240 patients in all. Half of the patients will be allocated to the treatment condition (*n* = 120) and the other half to the wait-list conditions (*n* = 120). Half of the patients in the wait-list condition wait 8 weeks, the other half wait 12 weeks before commencing treatment. Because the treatment is offered in an ordinary outpatient clinic, the duration of the treatment will vary. To control for potential differences in treatment duration the wait-list condition also contained two different conditions.

Guidelines from the Norwegian Directorate for Health and Social Affairs state that patients who fulfil the criteria for a moderate depressive episode according to ICD-10 have the right to specialised health care within 8 weeks of referral [45, 46]. Thus, patients with this diagnosis will be allocated evenly between the treatment condition and the 8-week waiting condition. No patients with moderate depressive episode will be allocated to the 12-week waiting condition due to Norwegian law.

The randomisation procedure is performed by administrative personnel who otherwise are not involved in the patient’s treatment. Clinicians are not involved in the randomisation procedure. The initial assessment session is carried out by a different therapist than the one the patient sees for treatment. Blinding the treatment therapist to group allocation is not doable for logistical reasons (e.g. date of journal documents). Assessment of diagnosis at end of treatment using the Mini-International Diagnostic Interview is carried out by an independent clinician who has no prior contact with the patient.

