### Retention and follow-up

We will strive to collect data on all patients, regardless of whether they complete treatment or not. The clinic has collected self-report questionnaires from patients for clinical use since its inception in 2007, and the infrastructure for data collection is well-established. For the post-treatment follow-up at 6, and 12 months, self-report measures will be mailed to the patient. Patients will also receive a reminder per SMS and a follow-up phone call. Data on sick leave will be collected from national registries and is thus less vulnerable to loss to follow-up.

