### Sample size estimate

Sick leave will be operationalised as a percentage of sick leave collected both from the national registry and self-report. To evaluate the intervention versus wait-list condition, the percentage of sick leave status of the intervention group will be compared at end of treatment to the status of the control group at the end of the waiting period. The minimum expected effect is that of the treatment reported in the naturalistic follow-up study at the same clinic [56]. Data from this study showed a self-reported full RTW response rate of 0.41 in the intervention group versus 0.26 in the wait-list control group, with a pooled standard deviation of 0.4 [34]. Given this result, to detect differences in a dichotomous outcome variable we would need approximately 120 in each treatment group to have an 80% chance of detecting a significant difference at a two-sided significance level of 0.05 [63]. For the anxiety and depressive symptoms, detecting a 5 point difference between intervention and waitlist control group using a pooled standard deviation of 6.95, we need approximately 31 participants in each of the group in order to have an 80% chance of detecting a significant difference at a two-sided significance level of 0.05 [28, 64].

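### The stated self-report schedule ties the wait-list arm's end-of-wait measurement to the first treatment session, so controls who never start treatment would have no BDI-II, BAI or self-reported sick leave at the comparison point

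*Protocol article*

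**What the plan says.** All references are to the Protocol article.

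- **Comparison point.** Under Sample size estimate, the treated arm's sick leave "will be compared at end of treatment to the status of the control group at the end of the waiting period". Under Randomisation and blinding, the wait has two lengths: "Half of the patients in the wait-list condition wait 8 weeks, the other half wait 12 weeks before commencing treatment".
- **Collection points.** Primary objectives: "Self-report data will be collected at initial assessment, start and end of treatment as well as at 6 and 12 months follow-up". Secondary objectives: "The questionnaires will be collected at screening, first treatment session and last treatment session", followed by questionnaires at 6 and 12 months after treatment. Control condition and concomitant care uses the same pattern for medication and service use: assessment, start of treatment, end of treatment.
- **Source of each outcome.** Primary objectives: "BDI-II and BAI are self-reported measures". For sick leave, "both national registry data will be collected from the National Labour and Welfare administration in addition to self-report". The registry window is given relative to the intervention, from 2 years before it to 4 years after it.
- **Retention.** The Retention and follow-up section states an intention to obtain data on every patient, including those who do not finish treatment. The procedure it describes is for the later visits: "For the post-treatment follow-up at 6, and 12 months, self-report measures will be mailed to the patient", with an SMS reminder and a phone call. It calls registry sick leave less vulnerable to loss.
- **Analysis.** Data analysis and data management plans intention-to-treat on all randomised patients, with a linear mixed model.

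**The concern.** The contrast needs each control's status on a calendar date, namely the end of the allocated 8 or 12 weeks. The listed self-report occasions are instead tied to treatment events. For a control, the only listed occasion that can serve as the end-of-wait measurement is the first treatment session.

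That makes the control outcome depend on attendance after a wait of 8 or 12 weeks. The intervention group is offered treatment within a week of assessment and has no such gap. A control who improved or went back to work during the wait plausibly has less reason to begin therapy. If some of these patients stay away, their BDI-II, BAI and self-reported sick leave are missing because the outcome was good, and the remaining controls look worse than the randomised group was.

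The stated analysis does not repair this. A control who never starts contributes only a baseline value. A mixed model then predicts that patient's end-of-wait score from attending controls with a similar baseline. It recovers the part of the loss that baseline explains, but not the part due to change during the wait.

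**Working it through.** **1. Schedule against comparison point**

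| Listed self-report occasion | Does it give an end-of-wait value for a control who never starts? |
|---|---|
| Initial assessment / screening | No, this is baseline |
| Start of treatment / first session | No, it does not take place |
| End of treatment / last session | No, it does not take place |
| 6 and 12 months after treatment | No, and there is no treatment date to count from |

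The retention statement is worded around completing treatment. It covers a patient who begins and stops, but sets no measurement date for one who never begins. The registry needs no attendance, so registry sick leave is not lost. Its window, however, counts from the intervention, which has no date for a control who never starts.

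**2. Inputs for a size illustration**

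- From Sample size estimate: full return to work 0.41 (intervention) and 0.26 (wait-list), 120 per group, symptom difference 5 points, pooled SD 6.95.
- Assumed, because the documents give no figure: the share *m* of the best-faring 26% of controls who are not measured, taken as 10, 20, 30 and 50%. Further assumptions are no other losses in either arm, normally distributed scores and, for symptoms, that the best 26% are the lowest scorers.

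The plan's own symptom figure reproduces: n = 2(1.960 + 0.842)² × 6.95² / 5² = 30.3, rounded up to 31 per group, as stated. The return-to-work sample size does not enter this check, except that 120 is the number of controls.

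**3. Symptoms (BDI-II, BAI)**

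The 26% point of the standard normal is −0.643, where the density is 0.324. The mean of the lowest 26% therefore lies 0.324 / 0.26 × 6.95 = 8.67 points below the control mean. If a fraction f = 0.26*m* of all controls is lost from this group, the observed control mean rises by f × 8.67 / (1 − f).

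**4. Complete-case full return to work**

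Observed control rate = 0.26(1 − *m*) / (1 − 0.26*m*). The apparent difference is 0.41 minus this rate. With no loss it is 0.41 − 0.26 = 0.15.

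| *m* | Controls lost of 120 | Rise in control symptom mean (points) | Observed control return rate | Apparent difference |
|---|---|---|---|---|
| 10% | 3.1 | 0.23 | 0.240 | 0.170 |
| 20% | 6.2 | 0.48 | 0.219 | 0.191 |
| 30% | 9.4 | 0.73 | 0.197 | 0.213 |
| 50% | 15.6 | 1.30 | 0.149 | 0.261 |

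The symptom shift is 0.23 / 5 = 5% to 1.30 / 5 = 26% of the planned difference. Both columns describe observed patients without a model, so a mixed model using baseline would remove part of the shift.

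**The case against.** Several points on the other side stand.

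- **Registry sick leave.** A reader might infer that the whole primary outcome of controls who return to work is lost. It is not: registry sick leave does not depend on attendance, so the gap concerns BDI-II, BAI and self-reported sick leave.
- **What is not visible.** The schedule figure is not shown, and the article condenses a fuller protocol. Questionnaires are already mailed before the screening session, so an end-of-wait mailing may have taken place. This limits the point to the text as written. Even so, the two sections that list the self-report occasions name none at the end of the wait, and this is a stated schedule rather than a detail left out.
- **Direction.** A reader might infer that the treatment effect is inflated. The documents do not establish it. They give no rate of declining treatment, controls who worsen or seek care elsewhere may also leave, and the intervention arm will have losses of its own. These are referred patients with a diagnosed disorder, so some who return to work will still want therapy. Bias towards treatment is likely, not proven.
- **Size.** With no true effect (0.26 in both arms), a complete-case test of return to work would reject about 6% of the time at *m* = 10% and about 53% at *m* = 50%. The higher figure should not be used as the trial's error rate. The loss is assumed, the planned analysis is a mixed model on continuous outcomes, and sick leave is the one domain with registry back-up.

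The intention-to-treat and retention statements do not answer the point, because neither creates a measurement for a control who never starts.

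**Conclusion.** The point holds for the self-report co-primary outcomes. Followed as written, the schedule yields no end-of-wait BDI-II, BAI or self-reported sick leave for a control who does not begin treatment, although the comparison is set at the end of the wait. The sample size section states that time point for sick leave; applying it to symptoms assumes the same contrast.

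The consequence is a risk of selective missingness, probably favouring treatment, whose size the documents cannot settle. Over the assumed 10–50% loss, the observed control symptom mean moves by about 0.2–1.3 points against a planned 5, and a complete-case return-to-work difference moves from 15 to 17–26 points. The low end is modest; the high end would matter. BDI-II and BAI are the most exposed because no second source exists for them. Registry sick leave needs only a usable reference date.

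**What to change.** **Rule.** Define the control outcome at the end of the allocated 8 or 12 weeks, whether or not treatment starts, and collect it with the mail, SMS and phone procedure already used for follow-up. Do the same at the planned end-of-treatment date for intervention patients who stop early.

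**Now that recruitment is complete:**

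1. Anchor registry sick leave to the end-of-wait date for all controls, and use it for those who never started.
2. Report, per arm, how many never attended a first session.
3. Add one missing-not-at-random sensitivity analysis for BDI-II and BAI, for example assuming that never-starting controls improved like controls who returned to work.
4. If an end-of-wait questionnaire was in fact sent regardless of attendance, correct the Primary and Secondary objectives sections to say so. That would largely settle the point.

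**Cost.** A registry look-up at a fixed date, a count and one extra analysis. The estimate may become slightly less favourable to treatment. In a trial still recruiting, the cost would be one mailing with reminders to controls who do not start.
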